**Statistical analysis:**

Data collected will be compiled on to a MS Office excel worksheet & will be subjected to statistical analysis using an appropriate package like SPSS software. Descriptive statistics like frequency (n) & percentage (%) of categorical data, mean & Standard deviation of numerical data in each group / subgroup will be depicted.

Frequency (n) & percentage (%) of various categories in each group / subgroup will be compared using chi square test.

Normality of numerical data will be checked using Shapiro – Wilk test or Kolmogorov-Smirnov test. Depending on the normality of data, statistical tests will be determined.

For a numerical continuous data following a normal distribution, inter group comparison (2 groups) will be done using t test, else a non parametric substitute like Mann Whitney U test will be used.

Intra group comparisons for a numerical continuous data following a normal distribution will be done using paired t test (for 2 observations) or repeated measures ANOVA for >2 observations, else a non parametric substitute like Wilcoxon signed rank test (for 2 observations) or Friedman’s test for >2 observations will be used.

Frequency (n) & percentage (%) of various responses in each time interval will be compared using chi square test / McNemar’s test.

Keeping alpha error at 5% and Beta error at 20%, power at 80%, p<0.05 will be considered statistically significant.

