# Material & Methods

## 3.1 STUDY DESIGN

Study design is single blind, randomized clinical trial.

Of the 2 groups running in parallel, the control arm will receive conventional treatment as per IMP, while the other group will receive homoeopathic intervention along with IMP. Allocation ratio will be 1:1 through randomisation obtained from computerised random number generator.

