### Duration of intervention:

28 days. However, if patient is discharged before, the medicines will continue, if needed, and the follow up will be done telephonically on the 14^th^ and 28^th^ day of illness.

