## TARGET SAMPLE SIZE:

Sample size was determined using the expected proportion of event / outcome in each group values of which are estimated from literature & using the formula,

n= (Z_α_ + Z_β_)^2^ [p q]

(p-q) ^2^

where Z_α_ is the z variate of alpha error i.e. a constant with value 1.96

Z_β_ i.e. a constant with value 0.84

p, q are proportions of the variable, values of which are taken from the parent article.

Approximate estimates:

1. 80% power
2. Type I error to be 5%
3. Type II error to be 20%
4. Difference in proportions between the groups to be 0.10

Substituting the values,

n= (1.96+ 0.84)^2^ [0.09)]

(0.10)^2^

n= 70.56

A minimum of **71 subjects per group** completing the study would be giving a good external validity. Since the number has to be equally divided in both the groups, **72 participants will be enrolled.**

For follow-up studies, to avoid loss by loss to follow up / attrition, kindly consider recruiting 5-25% more subjects so that even after attrition, we would be able to achieve the required minimum sample size.

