## STATISTICAL METHODS

Data analysis will be done through Intention To Treat (ITT) method, thus, all randomized patients should be included in the primary analysis. Additional analyses (e.g. subgroup analysis as per age, sex, perceived risk categories will also be carried out. Statistical advice will be sought before initiation. Kolmogorov-Smirnov tests will be used to analyse the normality of the data distribution. Data will be presented in number, percentage, Mean with 95% Confidence Interval, SD, Median, IQR. Statistical significance will be considered as the p value<0.05. Correlations between individual diagnoses/symptoms/ characteristics will be calculated in a Spearman rank correlation table. Correlations between groups of symptoms will be explored by principal component analysis (PCA). Comparison of baseline characteristics and outcome among all participants will be done by using parametric or non-parametric test. For categorical data χ2 exact test will be used. Concordance of the different methods for appraising result will be measured by Cohen’s kappa and Spearman rank correlation.

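### The between-arm tests for numerical outcomes use only patients with a value at one visit, which does not deliver the all-randomised promise when loss of MRI values is likely to be related to outcome

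*Protocol*

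**What the plan says.** **Methods.** The Statistical analysis section states that for normally distributed numerical data "inter group comparison (2 groups) will be done using t test", with Mann-Whitney otherwise. Within each arm it names "paired t test (for 2 observations) or repeated measures ANOVA for >2 observations", with Wilcoxon signed rank or Friedman as substitutes. Categories are compared by chi-square. No method compares the arms across visits.

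**Population.** The Synopsis sets the primary efficacy analyses in the ITT population, and Statistical Methods adds that "all randomized patients should be included in the primary analysis".

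**Outcome and schedule.** Section 3.6 makes change on contrast MRI the primary outcome, without fixing a scale. The Laboratory Investigations table places sinus MRI at D0, D14 and D28, and allows it earlier or later as required.

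**Who may lack an MRI value.** Section 3.5 withdraws patients whose disease spreads beyond the inclusion range, who need ventilation, or who are unwilling or non-compliant. Under Duration of intervention, a patient discharged early is told that "the medicines will continue, if needed, and the follow up will be done telephonically" at days 14 and 28. Target Sample Size mentions recruiting 5-25% extra to cover attrition.

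**The concern.** A t test or Mann-Whitney test at one visit takes in only the patients measured at that visit. A patient with a Day 14 MRI but none at Day 28 contributes nothing to a Day 28 comparison, although the Day 14 value says much about the missing one.

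The likely losses here are tied to how the patient is doing. Worsening leads to withdrawal. Recovery leads to discharge and a telephone call, which yields no image if it replaces the scan. The patients left at Day 28 may therefore be selected on outcome. If the selection differs between the arms, which a real treatment effect would itself cause, the comparison is no longer the randomised one. A true effect could be diluted, or an effect shown where there is none, while the report describes the analysis as ITT.

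**Working it through.** **The plan's own figure.** The protocol gives no figure on missing data. Its sample size reproduces from the printed formula: (1.96 + 0.84)² × 0.09 / 0.10² = 7.84 × 0.09 / 0.01 = 70.56. It rests on "Difference in proportions between the groups to be 0.10", so the trial is sized on proportions. The step from 71 per group to 72 in total is a separate matter; the planned 36 per arm is used below.

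**Numbers left.** If 5-25% is read as overall attrition, the patients with a final value number 36 × 0.95 = 34.2 down to 36 × 0.75 = 27.0 per arm.

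**Numerical score, best responders lost.** Assumptions, none from the protocol: normal improvement scores with SD 1, true effect 0.5 SD at both visits, D14-D28 correlation r = 0.7, and no D28 value when D14 improvement exceeds a common cut-off c. Among patients still observed, the mean D28 value is

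μ − r × φ(c − μ)/Φ(c − μ), with μ = 0 for control and 0.5 for active.

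- *Cut-off at the control arm's top 10% (c = 1.282).* Control ratio: 0.1755/0.9000 = 0.195. Active ratio: 0.2939/0.7828 = 0.3755, so 22% of active patients are missing. Observed difference: 0.5 − 0.7 × 0.3755 + 0.7 × 0.195 = **0.37 SD**.
- *Cut-off at the control arm's top 25% (c = 0.674).* Control ratio: 0.3178/0.7500 = 0.424. Active ratio: 0.3929/0.5693 = 0.690, so 43% of active patients are missing. Observed difference: 0.5 − 0.7 × 0.690 + 0.7 × 0.424 = **0.31 SD** (0.31 to 0.32 in simulations at 36 per arm).
- A likelihood-type estimate that also uses D14 recovers 0.50 SD in both cases.
- With no true effect, the same cut-offs give a difference of about zero and a type I error of about 5%.

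**Numerical score, worst patients withdrawn.** The model is the same, but the patients worst at D14 are withdrawn.

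- True effect 0.5 SD, one common threshold (25% of controls, 12% of active patients withdrawn): 0.5 − 0.7 × 0.424 + 0.7 × 0.227 = 0.36 SD (0.37 in simulation).
- No true effect, equal withdrawal (10%/10% or 25%/25%): bias about zero, type I error about 5%.
- No true effect, unequal withdrawal (control/active 15%/5%, 25%/10%, 25%/5%): bias of 0.12, 0.16 and 0.22 SD, with type I error 8.3%, 9.7% and 14.6%. Because more poor outcomes are removed from control, this bias makes the active arm look worse. Exchanging the two rates reverses it and gives a false benefit.
- The estimate using all observed data had bias of at most 0.01 SD throughout.

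**MRI response as a proportion.** Suppose all withdrawn patients are non-responders and are left out. The observed rate is then (true rate)/(1 − share withdrawn).

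| True control / active | Withdrawn control / active | Observed difference |
|---|---|---|
| 60% / 60% | 25% / 25% | 80.0 − 80.0 = 0 points |
| 60% / 60% | 25% / 10% | 66.7 − 80.0 = −13.3 points |
| 60% / 60% | 10% / 25% | 80.0 − 66.7 = +13.3 points |
| 60% / 70% | 25% / 15% | 82.4 − 80.0 = +2.4 points |
| 60% / 70% | 15% / 25% | 93.3 − 70.6 = +22.7 points |

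A true gain of 10 points can thus appear as 2 or as 23.

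**The case against.** **Missing-data rules usually belong in an SAP.** The protocol never states that patients with gaps are dropped. Imputation followed by a t test would satisfy both of its statements, and it says statistical advice will be sought. This stands in part: an SAP not shown may add such a rule. But the protocol itself names the tests, and without such a rule they do not include everyone randomised.

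**A reader might infer that the repeated measures ANOVA and Friedman tests bias the treatment effect.** They do not. They are within-arm analyses, and any between-arm bias comes from the t test or Mann-Whitney.

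**The primary outcome may not be numerical.** This stands. The MRI scale is not fixed and the sample size uses proportions, so chi-square may be the primary test. A linear mixed model alone could miss the primary analysis.

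**Telephone follow-up does not cancel the scan.** This also stands. The text leaves open whether discharged patients are imaged. If the call does replace MRI from day 14 onward, a patient discharged before then has no post-baseline image, and a mixed model adds nothing for that patient. Withdrawal under Section 3.5 is the more explicit source of outcome-related loss.

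**A reader might apply 5-25% to each visit separately,** which would leave 36 × 0.75² = 20.25 complete cases per arm. The protocol gives it as one overall recruitment allowance, so 34.2 to 27.0 is the supported range. The scenario with 43% of active patients missing lies well beyond that allowance and is an upper illustration.

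**Conclusion.** The point holds in a limited form. As written, the between-arm tests for numerical outcomes do not deliver the promised analysis of all randomised patients, and the protocol's own withdrawal and discharge rules make outcome-related gaps in the D14 and D28 MRI likely. The methods should be changed.

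Bias is possible, not certain. In the scenarios assumed, a true 0.5 SD is seen as 0.37 to 0.31 SD when the best responders are lost, and as about 0.36 SD when the worst are withdrawn at a common threshold. With no true effect, and loss equal and similar in kind, bias is about zero and type I error stays near 5%. A false effect in the null scenarios needs withdrawal that differs between arms, and can then run either way. The missingness rates, the correlation and the effect are all assumptions, so these figures show what can happen and do not predict this trial's result.

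**What to change.** 1. **Numerical outcomes measured at D0, D14 and D28.** In Statistical analysis, make the between-arm analysis a linear mixed model for repeated measures with arm, visit, arm-by-visit interaction and baseline value, unstructured covariance, and all observed values from all randomised patients. Take the arm difference from this model.
2. **MRI response analysed as a proportion.** Keep all randomised patients in the denominator, and count death, progression or withdrawal for worsening as non-response.
3. **Sensitivity analysis.** Add one for patients with no post-baseline MRI, or whose values are missing because of death or progression. The mixed model does not settle these cases.
4. **Follow-up wording.** Reconcile Duration of intervention with the imaging schedule, so that it is clear whether the telephone contact replaces the MRI.

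**Cost.** These are wording changes in the statistical and follow-up sections and slightly more analysis work. The analysis changes need no extra patients or visits, and SPSS, which the protocol names, fits the model. The drawback is that the mixed model assumes missingness depends only on observed data, which is why item 3 is needed.

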## PHASE OF TRIAL:

Phase II

## ESTIMATED DURATION OF TRIAL:

3 months

## DURATION OF ADMINISTRATION

30 days

## DATA COLLECTION METHODS

Considering the critical importance of COVID related ROCM , data from the trial participants will be collected extensively. All the below mentioned documents will be developed and retained.

- CRF of covid related ROCM.
- A database that stores the above information for each patient with the subsequent observations by the physician at every visit
- Reports of all laboratory investigations to help physicians understand efficacy of diagnostic tools and/or interventions.
- All data pertaining to homoeopathy, like case taking, repertorisation chart and prescription decisions will be maintained.

## STATISTICAL METHODS

Data analysis will be done through Intention To Treat (ITT) method, thus, all randomized patients should be included in the primary analysis. Additional analyses (e.g. subgroup analysis as per age, sex, perceived risk categories will also be carried out. Statistical advice will be sought before initiation. Kolmogorov-Smirnov tests will be used to analyse the normality of the data distribution. Data will be presented in number, percentage, Mean with 95% Confidence Interval, SD, Median, IQR. Statistical significance will be considered as the p value<0.05. Correlations between individual diagnoses/symptoms/ characteristics will be calculated in a Spearman rank correlation table. Correlations between groups of symptoms will be explored by principal component analysis (PCA). Comparison of baseline characteristics and outcome among all participants will be done by using parametric or non-parametric test. For categorical data χ2 exact test will be used. Concordance of the different methods for appraising result will be measured by Cohen’s kappa and Spearman rank correlation.

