Both Aspergillosis and Candida have been reported as the main fungal pathogens for co-infection in people with COVID-19^[[8]](#endnote-8)^ . Recently, several cases of mucormycosis in people with COVID19 have been increasingly reported world-wide, in particular from India. The primary reason that appears to be facilitating Mucorales spores to germinate in people with COVID-19 is an ideal environment of low oxygen (hypoxia), high glucose (diabetes, new-onset hyperglycemia, steroid-induced hyperglycemia), acidic medium (metabolic acidosis, diabetic ketoacidosis [DKA]), high iron levels (increased ferritins) and decreased phagocytic activity of white blood cells (WBC) due to immunosuppression (SARS-CoV-2 mediated, steroid-mediated or background comorbidities) coupled with several other shared risk factors including prolonged hospitalization with or without mechanical ventilators.^[[9]](#endnote-9)^ One of the systematic review showed that mucormycosis was predominantly seen in males (78.9%), both in people who were active (59.4%) or recovered (40.6%) from COVID-19. Hyperglycemia at presentation (due to pre-existing DM or new-onset hyperglycemia or new-onset diabetes or diabetic ketoacidosis [DKA]) was the single most important risk factor observed in majority of cases (83.3%) of mucormycosis in people with COVID-19, followed by cancer (3.0%).Studies suggested that covid-19 is associated with destruction of β-cell of the pancreas^[[10]](#endnote-10)^, ^[[11]](#endnote-11)^. History of corticosteroid intake for the treatment of COVID-19 was present in 76.3% of cases, followed by remdesivir (20.6%) and tocilizumab (4.1%). Commonest organ involved with mucormycosis was nose and sinus (88.9%), followed by rhino-orbital (56.7%) and ROCM type (22.2%). ^[[12]](#endnote-12)^ Uncontrolled hyperglycemia and precipitation of Diabetic Ketoacidosis is often observed due to corticosteroid intake. Low pH due to acidosis is a fertile media for mucor spores to germinate.

Moreover, steroid use reduces the phagocytic activity of WBC (both first line and second line defense mechanism), causes impairment of bronchoalveolar macrophages migration, ingestion, and phagolysosome fusion, making a diabetic patient exceptionally vulnerable to mucormycosis. COVID-19 often causes endothelialitis, endothelial damage, thrombosis, lymphopenia, and reduction in CD4+ and CD8+ level and thus predisposes to secondary or opportunistic fungal infection.^[[13]](#endnote-13)^

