## LABORATORY INVESTIGATIONS

| **INVESTIGATIONS** | | |
| --- | --- | --- |
| - **Lab parameters** | CBC, ESR, FBS, PPBS, HbA1C, LFT, KFT with electrolytes | D0 and as per IMP |
| - **Imaging technique** | - CEMRI of Brain with orbits and sinuses. | - (Only at inclusion) |
|  | - CEMRI PNS | - D0 (or latest report if it is within 03 days of enrolment day), D14 and D28, or before or after as per IMP/ requirement |
|  | - CT guided endoscopy-cum-biopsy Fungal smear/KOH staining | - As per IMP, if required |

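### Baseline characteristics are to be significance-tested at p<0.05, although randomisation makes that null true, while the named between-arm outcome tests are unadjusted and forgo precision available from D0 data (minor).

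*Protocol*

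**What the plan says.** The Statistical Methods section of the protocol puts baseline and outcome into one testing sentence: "Comparison of baseline characteristics and outcome among all participants will be done by using parametric or non-parametric test". It continues "For categorical data χ2 exact test will be used" and sets one threshold, "Statistical significance will be considered as the p value<0.05". Nothing there treats a baseline test differently from an outcome test. The sentence does not literally say that the comparison is between arms. In a two-arm trial, in a sentence that also covers outcome, that is the natural reading.

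The Statistical analysis section, which follows the sample size, names the between-group procedures: chi-square for categories, and a t test or Mann-Whitney test for numerical data. None carries a covariate.

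D0 data are plentiful. The Laboratory Investigations table lists "CBC, ESR, FBS, PPBS, HbA1C, LFT, KFT with electrolytes" at D0 and a contrast MRI of the sinuses at D0 (or a report from the preceding three days). ROCM stage 1 or 2 is established for eligibility. Allocation is 1:1 by computerised random numbers (section 3.1), with 36 per arm (synopsis).

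**The concern.** A significance test asks whether a difference could be due to chance. For baseline variables in a properly randomised trial the answer is already known: it is chance. The test can therefore mislead in two ways. Among many variables, some will probably cross p<0.05 and be reported as imbalances. In a trial this small, an imbalance in a prognostic factor can stay above 0.05 and be taken as evidence that the arms are comparable. Whether a covariate belongs in the analysis depends on how well it predicts outcome, and its baseline p-value does not measure that.

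What is at stake is mainly precision. Baseline data that could sharpen the treatment comparison are already collected, but the outcome tests named in the protocol do not use them as covariates.

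**Working it through.** **Inputs from the protocol.** 36 per arm (synopsis); p<0.05, taken as two-sided because the sample size uses 1.96; unadjusted two-group tests (Statistical analysis). **Assumed, because the protocol gives no figure:** the number of baseline variables tested, their mutual correlation, the covariate-outcome correlation ρ, and a continuous outcome with a 0.5 SD effect for the power illustration.

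**The plan's own figure.** The protocol gives no figure for baseline imbalance. Its only related calculation is the sample size, with "Difference in proportions between the groups to be 0.10": (1.96 + 0.84)² × 0.09 / 0.10² = 70.56, rounded up to 71. This reproduces. It is stated per group, whereas 72 are enrolled in total; that is a separate matter, and 36 per arm is used below.

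**1. Chance of at least one false imbalance.** For k independent tests this is 1 − 0.95^k. For correlated variables it was simulated with equally correlated normal variables.

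| k | independent | correlation 0.3 | correlation 0.5 |
|---|---|---|---|
| 10 | 40% | 35% | 29% |
| 12 | 46% | 40% | 32% |
| 14 | 51% | 44% | 35% |
| 20 | 64% | 54% | 42% |
| 25 | 72% | 61% | 47% |

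The items named in the protocol come to about 10 to 12: seven or eight laboratory entries, age, sex, risk category and (by assumption) ROCM stage. Testing the components of the blood count, liver and kidney panels separately could give 20 to 25. The range is therefore roughly 30% to 70%. Half is reached at log 0.5 / log 0.95 = 13.5 independent tests.

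**2. What a non-significant test lets through.** The standard error of a standardised difference is √(2/36) = 0.2357. The 5% critical value of t on 70 df is 1.994. The smallest significant difference is 1.994 × 0.2357 = 0.47 SD. A difference of 0.40 SD gives p = 0.09.

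Take an observed imbalance D = 0.40 SD. It shifts the unadjusted estimate by ρ × D. With m = ρD/0.2357 and s = √(1 − ρ²), the type I error of the unadjusted test, conditional on that imbalance, is P(Z > (1.96 − m)/s) + P(Z < (−1.96 − m)/s):
- ρ = 0.3: shift 0.12 SD, error 6.9%
- ρ = 0.5: shift 0.20 SD, error 10.0%
- ρ = 0.7: shift 0.28 SD, error 14.0%

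For any one covariate, about 15% of properly randomised trials of this size would show an imbalance above 0.3 SD that is still non-significant.

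**3. Precision forgone by the unadjusted tests.** For a 0.5 SD effect the unadjusted non-centrality is 0.5 / 0.2357 = 2.12, which gives power of about 55%. Adjustment divides the residual SD by raising the non-centrality to 2.12 / √(1 − ρ²).

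| ρ | non-centrality, adjusted | power, unadjusted | power, adjusted (simulated) |
|---|---|---|---|
| 0.3 | 2.22 | 55–56% | 59% |
| 0.5 | 2.45 | 55–56% | 67% |
| 0.7 | 2.97 | 55–56% | 83% |

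Adjusting only when the baseline test is significant gives about 55% to 57%, practically the same as not adjusting.

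**The case against.** The strongest reply is that baseline p-values change nothing in the treatment comparison. The protocol does not say that a significant baseline test triggers adjustment, or that a non-significant one will be read as proof of comparability. A reader might infer that the baseline test decides the analysis and so costs power. The documents do not support this. The planned outcome tests are unadjusted whatever the baseline shows, and a test-then-adjust rule would lose nothing against them. The gap in step 3 is the benefit of adjustment, not a cost of baseline testing. This part of the reply stands.

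A reader might also infer that baseline data are used only for testing. That is not so: age, sex and risk category define subgroups, and the D0 MRI enters the primary outcome, which is a change on imaging. Nor is a false imbalance about half the time a figure from the protocol, because it depends on how many variables are tested.

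It is tempting to use hyperglycaemia as the example, since the Background says that it "was the single most important risk factor observed in majority of cases (83.3"%. That describes who develops mucormycosis. It is not evidence that hyperglycaemia predicts MRI change in stage 1 or 2 disease.

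Chance imbalance is also random error, already covered by the overall 5% level. The percentages in step 2 are conditional on the imbalance observed.

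Finally, covariates may be named in an SAP that is not at hand, so their absence from the protocol is not in itself an error. What remains is what the protocol does fix: baseline significance tests, and a set of between-arm tests that are all unadjusted.

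**Conclusion.** The point holds in a limited form and is minor. The planned baseline tests answer no useful question. They carry a roughly 30% to 70% chance of at least one false imbalance (assumed 10 to 25 variables, correlation 0 to 0.5), and at 36 per arm they pass differences of up to about 0.47 SD. They do not bias the treatment estimate, and removing them alone would alter no treatment result.

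The material gain comes from replacing the unadjusted comparison. Under an assumed 0.5 SD effect on a continuous outcome, power rises from about 55% to 56% to 59%, 67% or 83% at ρ of 0.3, 0.5 or 0.7. At the low end the gain is small. The size of the benefit therefore rests on how prognostic the chosen covariate is, which the protocol does not document, and it would differ if the MRI outcome is analysed as a category.

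**What to change.** Make three changes in wording:
1. Remove baseline characteristics from the testing sentence in Statistical Methods.
2. State that the baseline table will be presented by arm descriptively, without p-values.
3. Make the primary between-arm comparison a regression, of a type suited to the scale of the MRI outcome, adjusted for a short list of D0 covariates whatever imbalance is observed. The first choice is ROCM stage (1 v 2) or D0 MRI status. D0 HbA1c is optional, since its prognostic value is an assumption. Fix the list before any outcome data are seen by arm, and if an SAP exists, state the same there.

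The cost is one or two degrees of freedom and a regression estimate to report beside the simple test. Stage, D0 MRI and HbA1c are already collected, so no new data are needed.

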## 3.6 OUTCOMES

#### Primary:

Change in condition as seen in standard imaging or other diagnostic techniques:

- MRI contrast in ROCM cases

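### Spearman rank correlation is listed beside Cohen's kappa as a measure of concordance, but it ignores systematic differences between methods; for numeric readings it would be the only planned measure (minor)

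*Protocol*

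**What the plan says.** The last sentence of the protocol's Statistical Methods section reads: "Concordance of the different methods for appraising result will be measured by Cohen’s kappa and Spearman rank correlation". It does not name the methods to be compared, say which coefficient goes with which type of reading, or say which one counts if they differ.

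The same section uses Spearman for a different purpose: "Correlations between individual diagnoses/symptoms/ characteristics will be calculated in a Spearman rank correlation table". It also sets a general threshold: "Statistical significance will be considered as the p value<0.05".

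Section 3.6 gives the primary outcome as "Change in condition as seen in standard imaging or other diagnostic techniques", with contrast MRI as the only item listed beneath it. The only secondary outcome is survival during hospitalization. Concordance between methods appears in neither.

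**The concern.** Concordance asks whether two methods give the same result for the same patient. Spearman's rho asks whether patients who rank high on one method also rank high on the other. Two methods that both respond to disease will usually correlate, even if one always grades it more severely. Adding a constant to one method, or changing its scale in any increasing way, leaves rho as it was. Yet a systematic difference of that kind is one of the main things a concordance analysis has to detect.

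Two consequences follow from the sentence as written:

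- **Numeric readings.** Cohen's kappa does not apply to them, so rho would be the only planned measure of concordance.
- **Ordered grades.** Two measures stand side by side with no stated precedence, and they can point in opposite directions.

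At stake is how a reader interprets an additional analysis of the methods used to appraise the result. The treatment comparison is not at stake.

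**Working it through.** **Inputs.** The concordance sentence states no figure, so there is none to reproduce. The protocol's one computed figure, the sample size, follows from its own formula, (1.96 + 0.84)² × 0.09 / 0.10² = 70.56, but it does not enter this point. From the document I take the two named coefficients, the 0.05 threshold and at most 72 patients with paired readings ("72 participants will be enrolled"). The protocol gives no method-comparison data, so every data pattern below is an assumption.

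**1. Four equally frequent grades (0 to 3); method B reads one grade above A, capped at 3.**

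- Exact agreement occurs only in grade 3: 0.25.
- B's grades 0, 1, 2, 3 have frequencies 0, 0.25, 0.25, 0.50. Chance agreement = 0.25 × (0 + 0.25 + 0.25 + 0.50) = 0.25.
- Unweighted kappa = (0.25 - 0.25) / (1 - 0.25) = 0.
- Linear-weighted kappa: mean observed disagreement is 0.75 grade. The mean expected by chance is 0.25 × 1 + 0.25 × 1 + 0.50 × 1.5 = 1.25. Kappa = 1 - 0.75/1.25 = 0.40.
- Spearman's rho, with 18 patients per grade: centred mid-ranks are -27, -9, 9, 27 for A and -27, -9, 18, 18 for B. The sum of products is 1458 and the sums of squares are 1620 and 1458. So rho = 1458 / √(1620 × 1458) = √0.9 = 0.95.

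**2. The same shift without a cap (B always exactly one grade higher, on a five-grade scale).**

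- Exact agreement 0%; rho = 1.00.
- Chance agreement = 3 × 0.25 × 0.25 = 0.1875. Unweighted kappa = (0 - 0.1875) / (1 - 0.1875) = -0.23.
- Linear-weighted kappa = 1 - 1/1.5 = 0.33. Quadratic-weighted kappa = 1 - 1/3.5 = 0.71.

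**3. Binary readings, 72 patients, every A-positive also B-positive.**

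| Positives, A v B | Agreement | Kappa | rho | p for rho |
| --- | --- | --- | --- | --- |
| 36 v 66 | 42/72 = 58% | 0.17 | 0.30 | 0.010 |
| 20 v 60 | 32/72 = 44% | 0.14 | 0.28 | 0.018 |

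At 72 pairs, any |rho| above about 0.23 is significant at two-sided 0.05, so a significant rho is compatible with poor agreement.

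**4. Numeric readings: A with mean 20 and SD 5; B = A + 10 + noise with SD 2 (a shift of 2 SD).**

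- Rho = 0.92 (simulated).
- Lin's coefficient = 2 × 25 / (25 + 29 + 10²) = 50/154 = 0.32.
- Bland-Altman: mean difference 10, 95% limits 10 ± 1.96 × 2, that is 6.08 to 13.92. The shift is visible at once.

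In examples 1 to 3 the planned unweighted kappa is low or negative and would show the disagreement. In example 4 nothing in the plan would show it.

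**The case against.** The strongest reply is that kappa is named first in the same sentence. For categorical readings it does its job, and a high rho beside a low kappa is itself the signature of a systematic shift. That stands, and it confines the point to numeric readings and to the missing precedence for ordered grades. The protocol identifies no numeric pair of methods: contrast MRI, biopsy and KOH smear are given no numeric readings. But the sentence does not restrict the methods compared to categorical ones either, and the section on laboratory investigations lists numeric values.

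It can also be said that kappa weights and limits of agreement are details for a statistical analysis plan, and that the protocol promises statistical advice before initiation. That is fair for the weights, and their absence is no fault here. It does not cover naming an association measure as a concordance measure, which the protocol itself does.

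Three stronger readings are tempting and are not supported:

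- A reader might infer that systematically disagreeing methods would be reported as concordant. No rule in the protocol turns a significant rho into such a verdict. The 0.05 threshold is a general statement, and kappa would be reported too.
- A reader might infer that the concordance result is the evidence for accepting another technique in place of MRI in the primary outcome. Nothing links the two. Contrast MRI is the only item listed, and CEMRI PNS is scheduled at D0, D14 and D28, while endoscopy-biopsy and smear are done only if required.
- A reader might simulate shifted grades, find Spearman significant in every data set, and set that against a nominal 5%. With truly associated readings the null of no association is false, so this is power and not an inflated type I error.

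**Conclusion.** The point holds in limited form and is minor. Spearman's rho is a wrong choice for concordance because it is blind to systematic differences. In the assumed examples it stays at 0.92 to 1.00 for a one-grade or 2 SD shift. For categorical readings the damage is small, since kappa is also planned. For ordered grades the contradiction is real but partial once the ordering is credited: linear-weighted kappa is 0.40 with a cap and 0.33 without. For any numeric readings the gap is complete, because rho would be the only measure planned.

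The sizes rest on assumed grades, shifts and noise, since the protocol has no paired data from which to estimate them. That rho is unaffected by a constant shift needs no such assumption. The treatment comparison, the sample size and the type I error are not affected.

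**What to change.** In Statistical Methods, delete the reference to Spearman from the concordance sentence and state instead:

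- **Categorical readings:** percent exact agreement and Cohen's kappa with 95% CI. If the categories are ordered, use weighted kappa and name the weights in advance. The choice matters: in the uncapped example linear weights give 0.33 and quadratic weights 0.71, with no patient graded alike.
- **Numeric readings, if any are compared:** the mean difference with Bland-Altman 95% limits of agreement.

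Keep Spearman for the exploratory correlation table already described in that section.

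The cost is one sentence of wording and no new data. The drawback for the sponsor is that the reported concordance may look less favourable.
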